### Inclusion criteria for patients

• Age >18 years

• BP > 140/90 mmHg

Two consecutive measurements carried out in the practice

(measured by the general practitioner or practice assistant at the start of the study; both measurements must be greater that 140/90 mmHg with the second measurement qualifying for inclusion.

• Unchanged anti-hypertension treatment for one month before inclusion

• Patient able to measure blood pressure at home

• Written informed consent

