#### Sample Size

Case number calculation and power analysis were carried out on the basis of the expected effect for systolic blood pressure. With an alpha of 0.05 and a power of 0.9 (one-sided test) this means that 138 patients are required in order to be able to show a clinically relevant blood pressure difference of 7 mm Hg systolic with a standard deviation of 14 mmHg between the groups. Assuming a dropout rate of 20% this means that at least 166 patients are required.

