### Data collection

#### Primary end point

There will be blood pressure measurements by the general practitioner at the start (t0) as well as after 3 months (t1) and at the end of the study after 6 months (t2). To rule out blood pressure differences BP will be measured at both arms at t0. Each subsequent measurement in the practice of the general practitioner will involve two blood pressure measurements in each case in the left arm if the initial measurement did not differ between both arms by more than 5 mm Hg. If the measurement differed by more than 5 mm Hg at t0, BP will be measured at the arm with the higher reading subsequently. All the readings will be recorded, but for inclusion (as stated above) as ell as for analysis, the second measurement will be used. The difference (t2-t0) between the systolic blood pressure readings at the practice measurement represents the primary end point.

All patient contacts will be collected over the entire period. At time t2 (after the end of the study) the number of times there was contact with the general practitioner since the inclusion of the patient will be recorded.

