#### Analysis

At the end of the study the list with the booklet codes as well as the code, generated out of the patients' name and his birthday will be send to the study centre. In the study centre, all received questionnaires and lists will be scanned electronically and a TIF-file will be generated to avoid data manipulation. The data will be directly exported in the statistic program (STATA, version 9).

Descriptive statistics: average value with +/- 1 SD and median values of the average blood pressure readings for both groups. In accordance with the normal distribution test it will be decided whether parametric or non-parametric tests are to be applied. Treatment group comparisons for categorical data will be done with the χ^2 ^test. For continuous variables, comparisons between treatment groups were done with *t *tests.

Primary outcome: difference (t2-t0) between the systolic blood pressure average readings from the practice measurement. All patients will be analysed in accordance with the „intention-to-treat” approach and the latest available measurement will be used (last- observation carried forward). When interventions are provided via GPs, one should be aware of a cluster effect. We decided to perform a randomisation on the patient's level since the effect mediated by the GP on the intervention is assumed to be small. Nevertheless, we will account for that and include the factor "Practice" as a random effect in the analysis.

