#### Patient informed consent

Previous to study participation patients receive written and spoken information about the content and extent of the planned study; for instance about potential benefits for their health and potential risks. In case of acceptance they sign the informed consent form.

In case of study discontinuation all material will be destroyed or the patient will be asked if he/she accepts that existing material can be analyzed in the study.

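### Carrying the last observation forward as the primary missing-data rule scores patients lost before 3 months as no change, which shrinks the effect and can bias it if early dropout differs between arms

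*Protocol article*

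**What the plan says.** The primary end point is defined under Primary end point: "The difference (t2-t0) between the systolic blood pressure readings at the practice measurement represents the primary end point". Practice readings are planned "at the start (t0) as well as after 3 months (t1) and at the end of the study after 6 months (t2"), so t1 is the only visit between baseline and the final measurement.

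The Analysis section promises an intention-to-treat analysis of every patient and names one rule for missing values: "the latest available measurement will be used (last- observation carried forward").

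The baseline is a selected reading. Under Inclusion criteria for patients, "both measurements must be greater that 140/90 mmHg with the second measurement qualifying for inclusion". The same reading is the analysis baseline: "for inclusion (as stated above) as ell as for analysis, the second measurement will be used". The Analysis section speaks of average readings instead, but this changes nothing here, because both t0 readings had to pass the threshold.

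Dropout is expected. The Sample Size section begins its inflation with "Assuming a dropout rate of 20" per cent and arrives at 166 patients.

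Under Patient informed consent, the plan adds: "In case of study discontinuation all material will be destroyed or the patient will be asked", and the sentence goes on to let the patient agree that existing material is analysed.

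**The concern.** For a patient lost before t1, the latest available value is t0, so the primary outcome is t0 minus t0, which is zero. That is not a neutral value. Entry required a high reading, and such readings tend to fall on re-measurement in either arm, even if the booklet does nothing. The rule assumes that early dropouts stay at their entry level and treats that guess as an observation.

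Two things are at stake. With equal dropout, zeros in both arms pull the estimated difference towards zero. With unequal dropout, the arm that keeps more patients is credited with more of the common fall, which shows up as a treatment difference. Unequal dropout is possible here: general practitioners know the allocation (Blinding), and the booklet is meant to improve adherence (Hypothesis). If it also improves retention, the carry-forward rule turns retention into apparent blood pressure benefit, in the direction in which a one-sided test looks.

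**Working it through.** **Inputs from the protocol article.** Difference 7 mmHg, SD 14 mmHg, one-sided alpha 0.05, power 0.90, 138 patients, 20% dropout, 166 recruited (Sample Size). Visits at t0, 3 and 6 months (Primary end point). A 1:1 allocation is assumed, giving 83 per arm.

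**The plan's own figure.** n per arm = 2 × (1.645 + 1.282)² × 14² / 7² = 68.5, rounded up to 69, so 138 in total. This matches. The 166 is 138 × 1.2. With 20% lost, 166 × 0.8 = 132.8 remain, about 66 per arm. Their power for the full 7 mmHg is about 0.89 one-sided. That is the fair comparator for the carry-forward analysis.

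**Equal dropout.** Let d be the dropout proportion, s the share of dropouts who have a t1 reading, and f the fraction of the effect present at t1. The expected difference is

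7 × [(1 − d) + d × s × f].

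- All losses before t1 (s = 0): 7 × 0.8 = 5.6 mmHg.
- Half with a t1 reading showing half the effect (s = 0.5, f = 0.5): 7 × 0.85 = 5.95 mmHg.
- Half with a t1 reading showing the whole effect (s = 0.5, f = 1): 7 × 0.9 = 6.3 mmHg.

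**Power when all losses precede t1.** The zeros also change the spread. With SD 14 among completers and a common fall R (an assumption), the variance is 0.8 × 196 + 0.2 × 0.8 × (R + 7)² in the intervention arm and 0.8 × 196 + 0.2 × 0.8 × R² in the control arm. The table uses 5.6 mmHg, 83 per arm and one-sided 5%.

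| Assumed common fall R | Variances (intervention, control) | Pooled SD | Power |
|---|---|---|---|
| 0 mmHg | 164.6, 156.8 | 12.7 | 0.88 |
| 5 mmHg | 179.8, 160.8 | 13.1 | 0.87 |
| 10 mmHg | 203.0, 172.8 | 13.7 | 0.84 |

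Against 0.89 for completers alone, the rule itself costs about 0.01 to 0.05 of power in this extreme case.

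**Unequal dropout, all before t1.** With true difference D and dropout proportions dI (intervention) and dC (control), the expected difference is

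D × (1 − dI) + R × (dC − dI).

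The protocol article does not give R; 5 to 10 mmHg is assumed.

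| Dropout, intervention / control | D = 0 | D = 7 |
|---|---|---|
| 20% / 20% | 0 | 5.6 |
| 15% / 25% | 0.5 to 1.0 | 6.45 to 6.95 |
| 25% / 15% | −0.5 to −1.0 | 4.75 to 4.25 |
| 10% / 30% | 1.0 to 2.0 | 7.3 to 8.3 |
| 30% / 10% | −1.0 to −2.0 | 3.9 to 2.9 |

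Positive values favour the colour-coded booklet. The spurious part always favours the arm that loses fewer patients.

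**Is a common fall plausible?** Regression to the mean alone gives about 1.2 to 6.1 mmHg after selecting a systolic reading above 140 and up to 180. This assumes a population mean of 140 to 150, SD 16 and between-visit correlation of 0.5 to 0.8, none of which is in the protocol article. Routine care could add to it.

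**The case against.** The strongest defence is that the rule is roughly harmless under balanced dropout. Both arms meet the same entry criterion, so the common fall cancels, and with no true effect the expected difference is zero. The shrinkage is then conservative. All of this stands. Placing every loss before t1 is also the extreme case, since the 3-month visit softens the effect. And the 5.6 mmHg is an underestimate only if early dropouts would have gained as much as the others; if they gain nothing, part of the shrinkage is real.

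Three stronger readings are tempting, and the document does not support them.

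- A reader might infer that power falls to 0.82 one-sided, or 0.73 two-sided, from 0.90. The 0.82 keeps SD 14 although the zeros reduce the variance. The 0.73 is two-sided, while the plan's 0.90 is one-sided. The comparator should be the 0.89 available from completers.
- A reader might infer that the high entry reading biases the comparison by itself. It does so only if dropout is unequal or related to outcome. The article makes imbalance possible but does not predict it.
- A reader might infer that the consent section defeats the carry-forward rule because data are destroyed. The sentence also allows data to be kept and analysed with the patient's agreement. Honouring a withdrawal is a consent matter, and where data are destroyed no zero is imputed. It is a separate point of reconciliation.

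A statistical analysis plan may add sensitivity analyses. That does not answer the point, because carry-forward is already fixed as the primary rule.

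**Conclusion.** The concern holds in a measured form. Following the plan as written shrinks a 7 mmHg difference to between 5.6 mmHg (all 20% lost before 3 months) and about 5.95 to 6.3 mmHg (half with a 3-month reading showing 50% to 100% of the effect). This assumes equal dropout and the same average benefit in those lost. The power cost is small. The more serious risk is unequal early dropout, where the rule can move the estimate in either direction by the amounts tabulated; these rest on an assumed common fall and assumed imbalances. Even the largest spurious value, 2.0 mmHg, is modest against 7 mmHg. It is nevertheless avoidable, and it would be reported as treatment effect. The rule should be replaced before analysis, although it does not invalidate the trial.

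**What to change.** Make the primary analysis a likelihood-based linear mixed model of systolic pressure at t1 and t2, with treatment-by-visit, baseline systolic pressure, and random effects for practice and patient. Take the t2 treatment contrast as primary. Keep carry-forward as a sensitivity analysis and add one analysis that departs from missing at random, since carry-forward is a weak check on that assumption. Report dropout by arm, before and after t1.

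The cost is a change of analysis wording. The t1 reading is already collected and a practice random effect is already planned. The small downside is reliance on missing at random, which cannot be tested but is less restrictive than assuming that every early dropout stays at the entry reading.

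Separately, reconcile the Patient informed consent section with the Analysis section's commitment to analyse every patient, for example by stating that patients whose data were withdrawn at their request will be counted and reported by arm. This costs one sentence.

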## Discussion

Although there is a large amount of data on non adherence in chronic illnesses such as diabetes, heart failure, chronic lung disease and hypertension, there is relatively little research data on interventions which try to solve the problem of non-adherence. In addition, the conclusions of intervention studies are often based on subjective patient information and not on objective investigations. Data and evidence on a true change in behaviour assessed with hard clinical end points are needed.

Our study measures the use of a simple, practicable intervention tool. A new BP record booklet containing and providing a visualised interpretation in colour of blood pressure control that is useful as feedback for the patient and doctor and can help to improve patient-doctor communication as well as triggering appropriate behaviour strategies. A change or adjustment in behaviours is an important precondition to achieve relevant clinical end points in the case of chronic illnesses (improvement of adherence, reaching treatment targets, reduction in complications and secondary failures as well as lowering direct and indirect costs).

If there is evidence of a significant effect with this simple intervention and the new hypertension control tool, then this benefit can be achieved without additional treatment and risk of side-effects, without relevant additional costs and without additional effort for the patient and doctor. Patients, who measure their blood pressure at home generally, record their blood pressure. The documentation in a different record booklet as used previously therefore means no extra effort. The instruction for using the new blood pressure record booklet is also no extra effort for the "health professionals", in this case the general practitioner or practice assistant. No extra work load is an important condition for implementation of evidence based recommendations into practice.

### Limitations of the study

A double blind approach is not possible because training has to be given on the blood pressure record booklet. Some sub-groups (age stratification, gender, education) are too small to reach significance.

#### Ethical principles

The study is being conducted in accordance with medical professional codex and the Helsinki Declaration as of 1996 as well as Data Security Laws.

Study participation of patients is voluntary and can be cancelled at any time without provision of reasons and without negative consequences for their future medical care.

#### Patient informed consent

Previous to study participation patients receive written and spoken information about the content and extent of the planned study; for instance about potential benefits for their health and potential risks. In case of acceptance they sign the informed consent form.

In case of study discontinuation all material will be destroyed or the patient will be asked if he/she accepts that existing material can be analyzed in the study.

#### Vote of the ethics committee

The study protocol is approved by the ethics committee of Zurich (Kantonale Ethikkommission (KEK) Zürich (EK-1738).

#### Data security/disclosure of original documents

The patient names and all other confidential information fall under medical confidentiality rules and are treated according to appropriate Federal Data Security Laws. All study related data and documents are stored on a protected central server of the University of Zurich. Only direct members of the internal study team can access the respective files.

Intermediate and final reports are stored at the Department of General Practice at the Zurich University Hospital (USZ).

## List of abbreviations

HBPM: Home Blood Pressure Measurement; BP: Blood Pressure; KEK: Kantonales Ethisches Kommitee.
